### Ethics Approval

All procedures and informed consent were approved by the Scientific Ethics Committee of Health Science of Pontificia Universidad Católica de Chile. The study was approved on March 11, 2021, and renewed on January 6, 2022, with validity of 1 year (# 200813008).

### Incentives

The participants will not receive any incentive for participating in this study. An incentive equivalent to US $12 will be offered to participants who complete the postintervention assessment.

## Results

The adaptation of the face-to-face intervention to the eHealth format was carried out between March and July 2021, and enrollment began in August 2021. Enrollment and data collection will continue until 50 participants have been enrolled and their data collected. We expect to complete the enrollment in August 2022 and for the primary impact analysis to be conducted in December 2022.

## Discussion

### Expected Findings

The objective of this study is to assess the feasibility and acceptability of the C@nnected group videoconferencing intervention, which aims to improve maternal sensitivity in mother-infant dyads attending PHC centers in Chile and was adapted from a face-to-face intervention. We expect to find an adequate feasibility of this intervention in terms of achieving good recruitment rates (around 60% mothers will accept the invitation to participate in the study with respect to those who meet eligibility criteria), good adherence to group intervention (around 60% in the intervention arm will receive the intervention), and adequate adherence to the sessions (the average expected attendance is 3 out of 4 sessions). We expect to find a very good acceptability of the intervention with high scores in the satisfaction questionnaire and positive evaluation in the qualitative assessment. We also expect to find favorable results of the intervention in terms of clinical outcomes, especially relating to maternal sensitivity, which will allow us to estimate the sample size for the future RCT to evaluate effectiveness. The results of this study will inform the key parameters for the implementation and evaluation of the intervention and facilitate the design of an effectiveness study in the future.

The COVID- 19 pandemic has led health teams to adapt some interventions to the eHealth format, and it is likely that many of these interventions will remain in this format even after the pandemic is over. Nevertheless, we should not assume that interventions will work equally as well when delivered through virtual methods. Existing interventions must be carefully adapted and include a focus on identifying the core components that must be maintained [21].

Internationally, there are some group parenting interventions with proven efficacy to increase maternal sensitivity; however, one of the main problems of this type of intervention is low adherence [48]. The development of eHealth interventions may improve the accessibility and flexibility of group-based interventions, which are important for parents. If this group intervention delivered by videoconference is shown to be feasible, it will be particularly useful for mothers that face barriers to attending face-to-face interventions.

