## Methods

### Trial Design

This is a data analyst–blind, superiority, pilot feasibility study with a mixed design. The quantitative component is a 2-arm randomized parallel group of 50 mothers of infants aged 6-12 months who receive health care in 2 PHC centers in Santiago, Chile. Mothers will be randomized into the intervention or control group in a to 3:2 ratio (with more people allocated to the intervention arm). Both groups will receive the usual treatment and educational brochures provided by the PHC center, with the intervention group also receiving the C@nnected videoconferencing intervention. The qualitative component will consist of semistructured interviews with intervention providers to identify possible improvements and core components of the intervention as well as focus groups with mothers participating in the intervention to evaluate user acceptability and satisfaction with the implementation.

This type of study is suggested by the literature as an initial requirement for the implementation of an innovative intervention before applying it on a larger scale. It is also recommended to use quantitative and qualitative methodologies to evaluate feasibility and acceptability [29]. This clinical trial protocol follows the SPIRIT (Standard Protocol Items: Recommendations for Interventional Trials) and [30] and CONSORT (Consolidated Standards of Reporting Trials) guidelines [31]. Figure 1 provides a flowchart of the study process.

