#### Secondary Outcome Measures

Clinical outcomes measures will be carried out to characterize the sample and estimate how the intervention could guide the sample size of the next effectiveness study. These clinical outcome measures will be assessed at the preintervention assessment (t0) and 2 to 3 months later in the postintervention assessment (t1). Table 2 shows the schedule of enrollment, interventions, and assessments, and Figure 4 shows the study design schema.

**Table 2 table2:** Schedule of enrollment, interventions, and assessments.

Scheduled items		Study period				
		Enrollment	Preintervention assessment	Allocation	Intervention	Postintervention assessment
Time point		t0	t0			t1

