### Sample Size

As this is a feasibility study, no hypotheses will be tested, and a formal power calculation is not required [44,45]. However, the evidence suggests a sample size of 25 people per arm for a small effect size of 0.2, which is suitable for clinical feasibility trials [45]. Therefore, a sample size of 50 participants was established, and the 3:2 allocation was chosen considering possible partial adherence to the intervention.

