### Assignment of Interventions

#### Sequence Generation

To generate the random allocation sequence, we will use a computer software program called Studyrandomizer using permuted block randomization with a block size of 5 in a 3:2 ratio.

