### Data Analysis

For the quantitative analysis, descriptive statistics will be used for the clinical and sociodemographic variables of the groups, eligibility rate, recruitment, and adherence. Analysis of covariance (ANCOVA) will be used to determine differences in clinical outcomes between the groups. Data analysis will be conducted using SPSS Statistics 27 software (IBM Corp).

For the qualitative analysis, interviews and focus groups will be analyzed considering the conceptual basis of the Framework Analysis Approach [46], which is commonly used for thematic analysis of semistructured interview transcripts. It allows for the identification of commonalities and differences in qualitative data to draw descriptive and explanatory conclusions grouped around themes. It is different from Grounded Theory, which involves making systematic comparisons between cases to refine each topic and is aimed at generating social theory [47]. The Framework Analysis Approach is best suited to research that has specific questions, a limited time frame, a predesigned sample (eg, mothers and professionals participating in the intervention), and a priori issues (eg, evaluation of implementation of an intervention)

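### The future RCT is to be sized from this pilot's clinical results, which 30 versus 20 mothers cannot support for small effects, and the superiority and ANCOVA wording conflicts with the statement that nothing is tested

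*Protocol article*

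**What the plan says.** **Use of the clinical results.** The Objective section makes estimation of the between-group effect size a secondary aim. Secondary Outcome Measures says the clinical outcomes serve to characterize the sample and to "estimate how the intervention could guide the sample size of the next effectiveness study". Expected Findings looks forward to favourable clinical results, especially on maternal sensitivity, "which will allow us to estimate the sample size for the future RCT to evaluate effectiveness". Changes in Maternal Sensitivity names that construct, measured by the ESA, as the primary outcome of the effectiveness study. No section gives a minimally important ESA difference or any other basis for the RCT's size.

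**Testing or not.** Sample Size says that "no hypotheses will be tested, and a formal power calculation is not required". Trial Design calls the study a "superiority, pilot feasibility study with a mixed design". Data Analysis says ANCOVA "will be used to determine differences in clinical outcomes between the groups".

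**The concern.** An effect estimate from 50 mothers is too imprecise to carry a sample-size calculation if the true effect is small. Tying the calculation to favourable results adds a bias: the estimates that get used are on average too large, so the RCT comes out too small. Informing the next trial is a stated secondary aim, so the error would pass straight into it.

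The second strand concerns consistency within the document. Superiority belongs to a testing framework, and determining a difference implies a conclusion about it. Beside a statement that nothing is tested, the reader cannot tell whether the four clinical scales will be reported descriptively or as evidence of effect.

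**Working it through.** **Inputs from the article.** Sample Size: "Therefore, a sample size of 50 participants was established, and the 3:2 allocation was chosen considering possible partial adherence to the intervention". Sequence Generation: "permuted block randomization with a block size of 5 in a 3:2 ratio". Sample Size also says "the evidence suggests a sample size of 25 people per arm for a small effect size of 0.2".

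**Assumptions, because the article gives no value.** Two-sided 0.05; 80% power; a 1:1 RCT; baseline correlation r of 0.5 or 0.7; no loss to follow-up unless stated.

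**Step 1: the plan's own figure.** 2 × 25 = 50. A 3:2 split gives 50 × 3/5 = 30 and 50 × 2/5 = 20, which is ten full blocks of 5. The split reproduces. The pairing of 25 per arm with an effect of 0.2 is not a power calculation (power there is 10.5%), and the article does not present it as one.

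**Step 2: precision of the effect.** SE(d) = √(1/30 + 1/20) = 0.289. ANCOVA multiplies this by √(1 − r²).

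| Analysis | SE | Half-width, 1.96 × SE | Half-width with t (2.01 × SE) |
|---|---|---|---|
| Unadjusted | 0.289 | 0.57 | 0.58 |
| ANCOVA, r = 0.5 | 0.250 | 0.49 | 0.50 |
| ANCOVA, r = 0.7 | 0.206 | 0.40 | 0.41 |

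Every half-width is at least twice the 0.2 effect that Sample Size names. An assumed 20% loss (24 versus 16) widens the unadjusted figure to 0.63 (1.96 × SE).

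**Step 3: what that means for the RCT's size.** n per arm = 2 × (1.96 + 0.8416)² / d² = 15.70 / d². For the interval around an observed d, SE = √(1/30 + 1/20 + d²/100), unadjusted.

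| Observed d | 95% CI | n per arm at d | n per arm at upper limit | at lower limit |
|---|---|---|---|---|
| 0.2 | −0.37 to 0.77 | 393 | 27 | none finite |
| 0.5 | −0.07 to 1.07 | 63 | 14 | none finite |

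**Step 4: true power of an RCT sized on the pilot.** An estimate at or below zero gives no sample size, so sizing on the observed effect needs at least a positive estimate. That is the only selection applied here. I drew 400,000 pilot estimates from Normal(true d, SE), sized the RCT from each positive one by the formula in step 3, and computed its power at the true d as Φ(d / √(2/n) − 1.96). The share of estimates at or below zero is Φ(−d / SE). Each cell gives unadjusted / ANCOVA with r = 0.7.

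| True d | Pilot estimate ≤ 0 | Median true power | RCTs below 80% power |
|---|---|---|---|
| 0.2 | 24% / 17% | 49% / 64% | 66% / 60% |
| 0.3 | 15% / 7% | 66% / 75% | 59% / 54% |
| 0.5 | 4% / 1% | 78% / 80% | 52% / 50% |

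At a true d of 0.2, unadjusted, the median planned size is 188 per arm against the 393 needed, and the 10th to 90th percentiles run from 42 to 3,726.

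**Step 5: what the pilot can supply.** With 48 degrees of freedom the 95% limits for the pooled SD are √(48/χ²) = 0.83 and 1.25 times the estimate. For a fixed difference in ESA points, n scales with the SD squared, so it is known to within factors of 0.83² ≈ 0.70 and 1.25² ≈ 1.56. That is a workable planning range; the range in step 3 is not.

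**Step 6: the wording.** No hypotheses (Sample Size), a superiority study (Trial Design) and determining differences (Data Analysis) cannot all describe one analysis. Estimation with a confidence interval fits the first statement. The other two need changing to match it.

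**The case against.** **The point estimate is never named as the sizing rule.** Guiding the next sample size, and informing key parameters, could mean using the SD, correlation, retention and adherence. This stands as a limit on the claim: a reader might infer a stated rule to plug in the observed effect, and there is none. It does not remove the concern. Effect-size estimation is the stated aim, sizing is tied to favourable results, and no alternative basis appears.

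**The harm can be overstated.** This also stands in part. A reader might infer that the RCT would usually be badly underpowered. Harsher figures follow only from a cut-off for a usable estimate, such as an observed effect above 0.2, and the article contains no such cut-off. With all positive estimates used, the shortfall at a true effect of 0.5 is slight, and the planned ANCOVA reduces it further. Nor would a chance null end the programme under this plan, since the article has no stop/go rule on clinical outcomes.

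**The effect size is a secondary matter.** Correct. The primary outcomes are feasibility and acceptability, and the total of 50 is not at fault for them. The article also reports a completed, unpublished RCT of the face-to-face version, but does not say it will inform the sizing.

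**ANCOVA is a sound estimator, and no P value or alpha is planned in the text.** Both true. The fault lies only in the purpose attached to ANCOVA and in the superiority label. Detail on reporting may sit in a fuller document that is not shown.

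**Conclusion.** The concern holds as a wording-level correction that should be made. The article makes this pilot's clinical results the only named basis for sizing the RCT. At 30 versus 20 the effect is known only to within about ±0.58 SD unadjusted, or ±0.50 to ±0.40 with ANCOVA at the assumed correlations. Sizing on a positive estimate would leave median true power at 49% to 64% for a true effect of 0.2, 66% to 75% for 0.3, and 78% to 80% for 0.5. These figures rest on the assumed alpha, power and correlations, on full follow-up, and on reading the plan as use of the point estimate. The half-widths do not depend on that reading.

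The conflict between the superiority and ANCOVA wording and the no-hypothesis statement needs no assumption. The pilot's recruitment, procedures and primary outcomes are unaffected.

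**What to change.** - **Trial Design:** delete the word superiority.
- **Data Analysis:** say that ANCOVA will estimate the baseline-adjusted mean difference with its 95% confidence interval, with no test and no claim of effect.
- **Secondary Outcome Measures and Expected Findings:** say that the RCT will be sized on a pre-specified minimally important ESA difference. The pilot will supply the ESA SD (with its uncertainty), the baseline-to-t1 correlation, recruitment, retention and adherence.
- **Clustering by workshop:** if an intraclass correlation is reported, give its interval and do not use it as a firm planning value. About 30 mothers in groups of 3 to 6 make only some 5 to 10 groups (30/6 to 30/3).

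The cost is a few sentences, with no change to conduct or data. The one real task is that the team must choose and justify an important ESA difference before the RCT.

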### Limitations

This is a small pilot study in a highly vulnerable area of Santiago, Chile, so its results cannot necessarily be extrapolated to other contexts.

### Strengths

The main strengths of this study are as follows: 1) the intervention has proven effectiveness and was designed locally using a framework that was later adapted for the electronic format; 2) it will evaluate the acceptability and feasibility of the intervention both quantitatively and quantitatively; and 3) it will evaluate clinical outcomes. In our opinion, these are essential steps to take before conducting a randomized controlled study, and they will subsequently allow us to scale up this intervention in similar contexts once its effectiveness is evaluated.

### Conclusions

This study will lay the foundation for a randomized clinical trial to examine the effectiveness of an intervention to improve maternal sensitivity in mothers attending PHC centers.

## Abbreviations

ANCOVA: analysis of covariance
ASQ: SE- 2: Ages and Stages Questionnaires: Social-Emotional
CEQ: Credibility/ Expectancy Questionnaire
CONSORT: Consolidated Standards of Reporting Trials
EPDS: Edinburgh Postnatal Depression Scale
ESA: Escala de Sensibilidad del Adulto
MIDAP: Millennium Institute for Research on Depression and Personality
MPAS: Maternal Postnatal Attachment Scale
PHC: primary health care
RA: research assistant
RCT: randomized controlled trial
SPIRIT: Standard Protocol Items: Recommendations for Interventional Trials
TAU: treatment as usual
